## Abstract

**Background:**

The evaluation and management of acute vertigo presentations is challenging for both patients and physicians. Benign paroxysmal positional vertigo (BPPV), acute unilateral vestibulopathy (e.g., vestibular neuritis), and stroke are priority diagnostic considerations in this circumstance. Existing evidence can be used to guide the diagnosis and treatment, however high value care opportunities—such as the Dix-Hallpike test (DHT), canalith repositioning maneuver (CRM), and gaze stabilization exercises (GSE)—are often underused, while neuroimaging studies are often overused.

**Methods:**

This trial contains a health system focused stepped wedge intervention and an embedded individually patient randomized clinical trial. The study will start with a 6-month pre-intervention period. This will be followed by staggered intervention at the engaged EDs in 11 waves and then an approximately 6-month post-intervention period. Concurrently, patients will be recruited before and after the physician level intervention is implemented at each ED. Enrolled participants will complete baseline survey and then be randomized individually, stratified by sex, age, and medical center, to the intervention or control arm patient materials using central computerized randomization. The intervention arm will be sent intervention materials and the control arm will be sent the hospital’s standard post-discharge materials. The primary outcome of the physician-based part of the trial is use of evidence-based care practices during the index ED visit. The primary outcome of the patient focused part of the trial is the dizziness handicap index over 4 weeks.

**Discussion:**

The DIZZTINCT-2 trial addresses key areas of uncertainty in how to improve the care of emergency department patients with acute vertigo. In addition, follow up data on how much and how fast patients improved was needed. DIZZTINCT-2 will address these key knowledge gaps efficiently.

**Trial registration:**

Clinicaltrials.gov NCT05634902. Registered on November 2022.

## Introduction

### Background and rationale {6a}

#### Brief summary

DIZZTINCT-2 focuses on benign paroxysmal positional vertigo (BPPV), acute unilateral vestibulopathy (e.g., vestibular neuritis), and stroke, which have established evidence-based practices for evaluation and management: the Dix-Hallpike test (DHT), Canalith repositioning maneuver (CRM), and gaze stabilization exercise (GSE), and a stroke risk assessment. The premise is that these practices have not been adequately disseminated to ED providers and patients, leading to missed opportunities for effective and efficient care delivery. Emergency department providers have ranked dizziness as a top priority for decision support [10].

Building on the success of the intervention used in DIZZTINCT-1, which was associated with an increased safe use of BPPV tests and treatments and reduced use of head CTs in dizziness visits, DIZZTINCT-2 aims to scale-up the reach of the materials to non-academic site physicians, enhance the clinical topics, and add patient-self-management resources. DIZZTINCT-2 also evaluates patient-centered outcomes and includes both English and Spanish versions of patient materials [29].

#### Rationale

BPPV is the most common peripheral vestibular disorder, with a lifetime prevalence of ~10% [54]. BPPV accounts for 8% of individuals with moderate or severe dizziness [54]. Despite being labeled “benign,” BPPV patients experience significant inconveniences and disabilities during symptomatic periods [35, 54]. Nearly 1 in 4 BPPV patients stop driving, 1 in 3 miss work, and more than 3 in 4 seek medical consultation [54].

The DHT and CRM are the gold standard test and treatment for BPPV, supported by numerous randomized controlled trials and systematic reviews [4, 5, 13, 20, 21, 53, 56]. Despite this, DHT and CRM are underused, with 94–96% of the target population not receiving these procedures, due to misconceptions and difficulty remembering how to perform them [27, 30, 38, 39, 43, 54]. The DHT and CRM are for posterior canal BPPV, the most common type. Other tests and treatments are available for horizontal BPPV.

Optimal use of DHT and CRM can reduce unnecessary head CTs, which are often performed in 30–40% of BPPV visits, exposing patients to radiation, higher costs, and longer stays [27, 29, 33, 39]. Correct use of DHT also aids in diagnosing other disorders needing different treatments, such as vestibular neuritis and stroke [31].

#### Identification of BPPV: the Dix-Hallpike test (DHT)

The DHT is the gold standard test for BPPV [4, 13]. It is a simple bedside test (Fig. 1). A positive test is indicated by up-beating and torsional nystagmus lasting about 10–20 s. However, physicians may misinterpret results, calling the test positive for symptoms rather than nystagmus, or misdiagnosing BPPV with any observed nystagmus pattern [42, 45, 50]. Nystagmus can also be observed with other disorders on positional testing: vestibular neuritis has horizontal and persistent nystagmus typically also observed prior to positional testing,central disorders can have persistent down-beating nystagmus.

**Fig. 1 Fig1:**
[figure not shown]
The Dix-Hallpike test

#### Treatment of BPPV: the canalith repositioning maneuver (CRM)

The CRM is the evidence-based, multidisciplinary guideline-concordant treatment for BPPV [4]. The CRM is designed to move canaliths around and out of the posterior canal into to the central chamber of the inner ear, thereby resolving positional vertigo. The first two steps of the CRM are the same as the DHT. If the DHT is positive, three additional steps move the particles, via the influence of gravity, out of the canal [13].

#### Relevance and priority for this study

The topic is highly impactful due to the number of affected patients (BPPV lifetime prevalence is ~10% [54]), the efficacy of CRM [4, 13], and the potential for improvement in healthcare efficiency [32, 33, 41, 45, 54]. The study brings together experts from multiple disciplines to address a top priority for decision support associated with high unnecessary testing and low use of evidence-based practices [10, 32, 33, 41, 44, 54]. The project aims to improve the effectiveness and efficiency of care for BPPV and other vestibular disorders.

Frontline physicians have expressed a strong need for vertigo support, ranking it as the #1 topic in adult ED presentations [10]. BPPV is common, identifiable, and treatable at the bedside without laboratory or imaging studies, which are discouraged in guideline statements [4]. ED physicians have advocated for BPPV processes, stopping an ED-based trial for ethical reasons due to the effect size at interim analysis [8]. Our preliminary studies indicate high demand for BPPV intervention.

#### Supporting data

The scientific premise of DIZZTINCT-2 is based on prior work in DIZZTINCT-1 which defined the problems, created an implementation strategy and materials, and demonstrated that providers adopted the strategy [29]. DIZZTINCT-1 aimed to increase the use of DHT and CRM and promote a BPPV-centric approach to dizziness. The strategy was guided by the Consolidated Framework for Implementation Research (CFIR) and informed by ED provider interviews to identify barriers and facilitators to DHT and CRM use [9, 30].

The DIZZTINCT-1 stepped-wedge RCT found that the implementation strategy increased DHT or CRM use (odds ratio 2.44; 95% CI 1.42 to 4.20; *n* = 7635 visits) [29]. The DHT or CRM use increased from 7% in pre-intervention visits to 17% in post-intervention visits in the estimated target population with a high probability of BPPV diagnosis (1.5 to 3.5% among all dizziness visits) [29]. The strategy was safe, reducing head CT use (from 44 to 37%) and showing a trend toward lower hospital admission. No serious adverse events were related to DHT or CRM, and non-serious adverse events (nausea, vomiting, headache) were uncommon (<5% of visits) and resolved or improved. There was also a trend toward a lower rate of subsequent strokes after ED visits in intervention visits compared with control visits [29]. Qualitative analysis of provider interviews revealed that providers often had positive experiences using the materials and performing the DHT and CRM [29].

#### Limitations of DIZZTINCT-1 for scaling up

DIZZTINCT-1 had limitations that need to be addressed before widespread dissemination [29]. Low provider participation at non-academic facilities was a major issue. Academic facilities had higher participation presumably due to the learning culture and routine education activities. Providers suggested refining and enhancing the strategy to make it more convenient and resourceful. DIZZTINCT-1 did not assess patient outcomes, which will be evaluated in DIZZTINCT-2. DIZZTINCT-2 enhances the CME session, expands clinical topics, incorporates patient-oriented materials, and captures patient-oriented outcomes during follow-up.

#### Acute unilateral vestibulopathy (vestibular neuritis) and stroke-dizziness

DIZZTINCT-2 includes detailed information on vestibular neuritis and stroke-dizziness. It incorporates evidence-based methods to distinguish vestibular neuritis from stroke, including the BE-FAST guide to identify stroke warning signs (balance issues, eye problems, facial drooping, arm weakness, speech difficulty, and acute onset) and a nystagmus assessment with video examples for central patterns of nystagmus and vascular risk assessment [1, 3, 7, 11, 31, 55, 57]. The algorithm also guides physicians on using the evidence-based treatments for vestibular neuritis: gaze-stabilization and balance/walking exercises [19].

#### Patient materials for management of dizziness

Patient materials may be important to improve the delivery of evidence-based dizziness management and patient outcomes. In DIZZTINCT-1, providers suggested that patient materials could improve the value and use of resources. BPPV self-management is effective. However, previous evaluations of available online resources for BPPV showed that while they generally describe steps accurately, patients often find instructions confusing [4, 26]. DIZZTINCT-2 includes patient-oriented BPPV self-management educational resources, evaluated positively by patients on measures of attitudes, self-efficacy, and social norms [28]. Self-management of unilateral vestibulopathy (vestibular neuritis) with gaze-stabilization and balance/walking exercises is also supported by a multidisciplinary guideline [19].

#### Summary

DIZZTINCT-2 builds on the findings of DIZZTINCT-1 and seeks to broaden its reach by addressing opportunities to optimize care efficiencies and patient outcomes for dizziness in the ED. This project has the potential to lead to lasting positive changes in the clinical care of patients with dizziness. By expanding the scope and evaluating patient outcomes, DIZZTINCT-2 aims to effectively implement evidence-based management practices for vestibular disorders.

### Objectives {7}

To improve the current management of dizziness in the ED and patient outcomes by using a provider- and patient-based educational intervention and implementation strategy focused on vestibular disorders.

#### Objective 1 (ED-level)

To determine the impact of an enhanced BPPV-centric implementation strategy on DHT/CRM performance in dizziness visits, at academic and nonacademic EDs, using a randomized stepped-wedge design. The strategy targets physicians and includes enhanced provider materials, patient-oriented resources, local champions, an online educational session, and reminder system.

### Trial design {8}

We will conduct a stepped-wedge, randomized clinical trial of a multi-faceted educational and care-process based intervention designed to improve the guideline-concordant care of patients with BPPV in the emergency department. The overall design includes an ED-level implementation and embedded, patient-level dissemination strategies which will allow evaluation of both implementation and effectiveness outcomes. Our study design and proposed methods are aligned with methodological standards in a stepped wedge, randomized clinical trial. The overall study period will be approximately 24 months. The study will start with a 6-month pre-intervention period. This will be followed by staggered intervention at the 15 EDs in 11 waves (some medical centers will be paired based on the medical service area) and then an approximately 6-month post-intervention period. The order that each ED receives the intervention will be randomized. The intervention will be provided as a complete package during the month each hospital is randomized. Concurrently, patients will be recruited before and after the physician level intervention is implemented at each ED. Enrolled participants will complete a survey to obtain baseline information and then randomized individually, stratified by sex, age, and medical center, to the intervention or control arm using central computerized randomization. The intervention arm will be sent intervention materials via patient specified preferred electronic communication. The control arm will be provided with the hospital’s standard post-discharge materials.

## Methods: participants, interventions and outcomes

### Study setting {9}

We will examine the interventions during the course of providing usual care for dizziness visits at Kaiser Permanente Southern California Emergency Departments (EDs). KPSC is a large integrated health care system that provides comprehensive health care services for approximately 1 in 5 Southern California residents (~4.8 million members). Kaiser Permanente is the largest real-world care setting in the nation and an ideal environment for population based clinical and health services research. The member population is socioeconomically diverse and broadly representative of the racial/ethnic groups living in Southern California. The organization’s model of care and information infrastructure allows the generation of evidence to support practice decisions and improve clinical outcomes. The electronic medical record (EMR) system, implemented at all 15 KPSC medical centers by 2006, contains complete visit-level data on health services, medications, and outcomes. We have confirmed EMR availability of ED visit data since 2007 [15]. The billing system can identity health service use by members at non-KPSC facilities. Vital statistics are linked to all members and, death can be ascertained regardless of membership status after the index visit.

### Eligibility criteria {10}

#### ED-level

Age 18 years or olderDizziness as primary reason for visit and/or discharge diagnosis
KPSC membership in last 31 daysNo level 1 trauma codeNot a prisoner

#### Patient-level (additional to ED-level above)

Discharged home from ED or observationDizziness as primary discharge diagnosis (dizziness, vertigo, lightheadedness, or imbalance)English or Spanish speakerNot cognitively impairedNot previously enrolledCapacity to consent—assessed by the Older Adults’ Capacity to Consent to Research (OACCR) scale

### Who will take informed consent? {26a}

We will obtain a waiver of consent to screen medical records and to abstract information from visits meeting the inclusion/exclusion criteria. The risk from medical record review is no more than minimal risk.

Participants in the patient level intervention activities will undergo formal informed consent and electronically sign an informed consent form. Consent will be obtained using standard language and content as approved by the IRB and adjusted to the specific circumstances of this project. Consent will be available using a self-service survey sent to participants via email or text. The self-directed process has opportunity to call study team for questions.

### Additional* consent provisions for collection and use of participant data and biological specimens {26b}*

We do not collect biological specimens and data use is considered in the main consent.

## Interventions

### Explanation* for the choice of comparators {6b}*

#### ED level

The intervention is described further in 11a below. The standard care case is existing usual ED processes.

#### Patient level

The intervention is described further in 11a below. Patients allocated to control (standard care) receive routine ED discharge instructions and referral to KPSC general resources in dizziness.

### Intervention description {11a}

#### ED level

The overall education intervention is delivered at the medical center level. These consist of educational materials, educational sessions, checklists, preparing local champions, available dot phrases, and designing reminder systems. Educational materials will consist of a mobile friendly website, and printed posters and notecards. A local champion will be recruited and prepared to help with notification of providers, dissemination of print materials (posters, cards), notification of decision aids, and answering questions. Although investigators will use a standard approach and some components will be fixed local champions can adapt distribution and notification of materials.

#### Patient level

The intervention components are the patient-oriented website about the test and treatment for BPPV and gaze stabilization exercises for vestibular neuritis. The videos will include background information on BPPV and vestibular neuritis and video examples of self-performance of the Dix-Hallpike test, canalith repositioning maneuver, gaze stabilization exercises, and walking and balance exercises. Prior research has established the safety and potential effectiveness of self-treatment using the CRM and gaze-stabilization exercises.

SPIRIT guidance: Interventions for each group with sufficient detail to allow replication, including how and when they will be administered.

### Criteria for discontinuing or modifying allocated interventions {11b}

We did not set any formal criteria for discontinuing either the provider or patient facing interventions because they were low risk.

### Strategies to improve adherence to interventions {11c}

We plan to assess implementation fidelity in order to monitor adherence during the trial and in plans to give recommendations for implementation in other settings. Our fidelity assessments have both quantitative and qualitative components to capture clinical and strategy fidelity. The quantitative data is the use of the educational session, print materials, website, app, checklist, and electronic medical record reminders. The use data will directly inform the interpretation of necessary components. Qualitative data will be obtained from semi-structured interviews with key stakeholders. We will sample individuals to capture a range of experiences with the materials and strategy (e.g., high frequency resources users, low frequency resource users, local clinical leaders). We will use an interview guide developed with our multidisciplinary team to assess training uptake, adherence to content, quality of use in practice, barriers to use in practice, resource dosage, satisfaction, and site adaptations. Interviews with local champions will specifically seek to capture variability in the approaches to provider notifications. Regarding, participant (patient-level) follow up—we use a variety of communication methods (email, phone, text) and financial incentives to promote adherence to the data collection.

SPIRIT guidance: Strategies to improve adherence to intervention protocols, and any procedures for monitoring adherence (e.g., drug tablet return, laboratory tests).

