### Sample size {14}

#### ED level

The Kaiser Permanente Southern California study site is comprised of 14 ED facilities, which collectively had nearly 40,000 dizziness visits in 2017. We plan to collect data on these visits for approximately 24 months. Thus, for the ED-level strategy, we will evaluate documentation of the DHT and CRM in >80,000 dizziness visits anticipating an increase in volumes over time. We hypothesize that the proportion of target visits with DHT/CRM documentation will increase from 7% in the pre-intervention period to 17% in the post-intervention period based on the findings in our estimated target population in DIZZTINCT-1. Even small absolute increases in the frequency of use of the DHT/CRM in the target population are considered clinically meaningful because the DHT and CRM are simple from a resource standpoint, not expensive, low risk and highly effective in clinical trials. With a sample of 80,000 visits, our power to detect an increase in DHT/CRM use from 7% in the control visits vs 17% in the intervention visits will be effectively 100% based on a two-sided test for independent proportions considering clustering at 14 sites, an intraclass correlation coefficient (ICC) by provider of 22% for provider-level variability (from DIZZTINCT-1) and a significance level of 5% (Table 1). We will use a mixed effects model to account for secular trends, hospital- and provider-specific features, and the potential relative association of the various components with the outcome. We estimate that 20% of the annual sample is the target population (80,000 × 0.20 = 16,000 visits) based on best available evidence that showed about 20% of dizziness patients in a national sample have BPPV characteristics. Of the 16,000 visits, approximately 8000 will be pre-intervention visits and 8000 post-intervention visits. With these volumes, we expect 560 (8000 × 7%) visits with DHT/CRM documentation in the pre-intervention period and 1360 (8000 × 17%) in the post-intervention period. Thus, we anticipate at least 1900 visits with DHT/CRM documentation. For modeling purposes, we should be able to easily meet and exceed the general rule of having 10 outcomes for each independent variable to avoid over-fitting. The large number of visits and anticipated outcomes will allow us to more closely examine differences at hospitals and provider types, and the relative influence of the various intervention components. We will be able to monitor use of the CME session, website, app, and reminder system and incorporate these variables in the model specific to the provider. The additional power will allow us to examine differences at hospitals and provider types, and the relative influence of the various ED-level implementation strategies.

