## Assignment of interventions: allocation

### Sequence generation {16a}

#### ED level

The overall study period will be approximately 24 months. After the 6-month pre-intervention period, the sites will receive the intervention in 11 waves. The order will be determined by using a random number generator. The intervention start date at each ED is the date the physicians are auto enrolled for the online CME and the printed education materials (i.e., posters, notecards) are distributed on site.

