### Methods in analysis to handle protocol non-adherence and any statistical methods to handle missing data {20c}

Many participants will not complete all 4 surveys; however, the longitudinal models planned for the primary analyses above should account for this. When appropriate, multiple imputation will be used. Exploratory analyses may focus on how many physicians at a site used the CME intervention and if possible, we will conduct analyses evaluating the primary outcome within the subset of physicians who viewed the CME.

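### Physicians' own use of a package delivered whole cannot show which components are necessary: if use tracks prior inclination, a component with no effect could show an odds ratio away from 1

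*Protocol article*

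**What the plan says.** Trial design {8} delivers all components to an ED together: "The intervention will be provided as a complete package during the month each hospital is randomized". Under Intervention description {11a}, ED level, "some components will be fixed local champions can adapt distribution and notification of materials". Under Sequence generation {16a}, ED level, the start date is when "the physicians are auto enrolled for the online CME" and print materials are distributed. Enrolment in the CME is thus automatic, but viewing is not assigned.

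Three places then use the resulting variation in uptake:

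- Strategies to improve adherence {11c}: "The quantitative data is the use of the educational session, print materials, website, app, checklist, and electronic medical record reminders". The next sentence reads: "The use data will directly inform the interpretation of necessary components". The section's aims include recommendations for other settings, and it also plans interviews with key stakeholders.
- Sample size {14}, ED level: the team will "monitor use of the CME session, website, app, and reminder system and incorporate these variables in the model specific to the provider". The purpose is described once as the components' relative association with the outcome and elsewhere as their relative influence.
- Methods for non-adherence and missing data {20c}: if possible, "we will conduct analyses evaluating the primary outcome within the subset of physicians who viewed the CME". This is introduced as exploratory and names no comparator.

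None of these places mentions self-selection into use.

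**The concern.** To call a component necessary is to say what would happen without it. No ED is assigned the package minus a component, so the randomisation does not inform that question. What remains is variation in uptake within rolled-out EDs, which arises from physician choice and from how champions distribute and notify.

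If physicians already inclined to perform the DHT/CRM use the materials more, the use coefficient mixes their inclination with any effect of the component. A random physician intercept does not cure this, because it assumes that the physician effect is independent of the covariates. The large sample narrows the interval around the estimate without removing the bias. At stake are the ranking of components and the advice to other health systems on which to keep.

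**Working it through.** **The plan's own figures.** The protocol gives no figure for component effects. The 22% ICC enters only the ED-level power calculation. Table 1's minimum sizes of 468, 2028 and 7800 visits reproduce exactly from a Hussey-Hughes stepped-wedge variance with 12 clusters, 13 periods, total variance 0.07 × 0.93, ICC 0.22 and two-sided alpha 0.05: 3, 13 and 50 visits in each of 12 × 13 = 156 cells, with power 0.813, 0.824 and 0.804. (The accompanying text says 14 sites; 12 appears in the text before Table 3.)

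**Inputs from the protocol.** Provider ICC 22% (Sample size {14}, ED level). Package odds ratio 2.44, and DHT/CRM use of 1.5% rising to 3.5% among all dizziness visits (Supporting data).

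**Assumptions, not in the protocol.** The ICC is read on the logit scale. Half of physicians use the component. r is the correlation between inclination and the latent tendency to use. Physician numbers, visits per physician and the spread of response are also assumed. The component's true effect is nil.

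**Step 1, physician SD.** Variance = (0.22/0.78) × π²/3 = 0.93, so SD = 0.963 on the logit scale.

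**Step 2, closed form.** With half of physicians using, users and non-users differ in mean standardised inclination by 2 × 0.7979 × r. The spurious odds ratio is exp(0.963 × 1.596 × r): 1.17 at r = 0.1, 1.36 at r = 0.2 and 1.59 at r = 0.3. This applies when use is a fixed physician trait or only post-rollout visits are compared.

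**Step 3, simulation of random-physician-intercept logistic models** (12 replicates per setting, so range ends are approximate). Rows 1, 2 and 5 use 400 or 800 physicians, 10 to 50 visits per physician per period and package odds ratio 2.44. Rows 3 and 6 use 300 to 600 physicians, 67 or 133 visits per physician-period and the 1.5% to 3.5% rates. Rows 4 and 7 use that second model with 300 physicians.

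| Row | Model and coding | Assumption | Odds ratio of a null component |
|---|---|---|---|
| 1 | Use as physician trait, or post-rollout only | r = 0.1; 0.2; 0.3 | 1.13–1.22; 1.34–1.43; 1.57–1.66 |
| 2 | Use switched on at rollout, pre-rollout visits included | r = 0.1; 0.2; 0.3 | 1.03–1.11; 1.07–1.21; 1.11–1.34 |
| 3 | As row 2, low rates | r = 0.3; 0.5 | 1.21; 1.29–1.43 |
| 4 | As row 3 | r = −0.3 | 0.84 |
| 5 | As row 2, users also respond more to the rest of the package | r = 0.2; response SD 0.5 logit, correlation with use 0.2–0.4 | 1.35–1.72 |
| 6 | As row 3 plus an ever-user term | equal response | 0.96–1.02 |
| 7 | As row 6, users respond more | r = 0.3; response as in row 5 | 1.17–1.34 |

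At r = 0 with equal response the odds ratio is 1.0. Within row 2 the bias shrinks as visits per physician rise, because pre-rollout visits anchor each intercept.

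**Step 4, what the ever-user term leaves.** A within-physician contrast cancels inclination but keeps the difference in response, roughly exp(0.5 × 1.596 × c), where c is the correlation between response and use. This is 1.17 at c = 0.2 and 1.38 at c = 0.4, in line with row 7.

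**The case against.** The best defence is that the protocol claims less than this implies. The sentence about necessary components sits in a fidelity section, says that use data inform interpretation, and is followed by interviews with high- and low-frequency users, local leaders and champions. The sample-size section once says association. The CME-viewer analysis is exploratory and conditional. The model is only outlined as mixed effects with provider-specific features, so the coding of use and any adjustment for prior rate may be set in an analysis plan. Not all use is physician choice either: record reminders are system-delivered and champions distribute print.

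Most of this stands. A reader might infer that use data alone are meant to decide which components are necessary; the text does not say so. It does not defeat the point, because the protocol itself sets out the inference, the use variables and the subset. Relative influence and necessity go further than its own wording of association, and adaptation by champions is not random either.

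The sign is also open. The Rationale attributes underuse to misconceptions and difficulty remembering the manoeuvres, so physicians who seldom perform them could be the heavier users. A useless component would then look harmful (row 4).

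**Conclusion.** The protocol states an inference about components that its design cannot identify. The bias arises if use is correlated with prior inclination or with responsiveness to the rest of the package. With the 22% provider ICC read on the logit scale, a null component could show an odds ratio of about 1.03 to 1.7 under the assumed positive correlations or differential response, and below 1 (0.84 at r = −0.3) under a negative one.

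Three stronger readings are tempting and unsupported:

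- That a null component would certainly appear to work, or would do so by a definite amount. The protocol gives no correlation, uptake rate or physician count.
- That the trial's main ED-level result is compromised. The randomised overall intervention effect is unaffected.
- That an ever-user term fully cures the problem. It removes baseline inclination only.

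This is a low-severity point about secondary and exploratory interpretation.

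**What to change.** For component analyses, add an ever-user term or a physician fixed effect next to current use, so that the use coefficient is each physician's change from his or her own pre-crossover level, with calendar time estimated from all physicians. For the CME-viewer subset, take the viewers' own pre-crossover visits as the comparator. State that this removes baseline inclination but not differential responsiveness to the rest of the package, and report the results as non-randomised associations. In Strategies to improve adherence {11c} replace the reference to necessary components, and in Sample size {14}, ED level, the references to relative influence, with association wording.

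The pre-crossover record data are already collected and the primary analysis does not change. The cost is less precise component estimates and a weaker claim about components.
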